#### Entomological

Transmission parameters in the 2 arms of the study will be estimated from measurements made throughout the 2 transmission seasons.

Primary: the EIR for *An. gambiae* s.l. and *An. funestus*/light trap/night inside sleeping rooms.

Secondary: (i) change in the prevalence (% mortality using diagnostic dose) and strength (LC50 value) of resistance to permethrin in each study arm throughout the study; (ii) the fertility and fecundity of adult female *An. gambiae* s.l. collected inside houses in both study arms.

Tertiary: (i) the relative abundance of different anopheline species and forms in light traps collected in each arm of the trial; (ii) the parity of *An. gambiae* to measure mean population longevity.

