## Background

Enormous progress has been made in the control of malaria in sub-Saharan Africa over the past decade [1,2]. A significant part of this achievement has resulted from a large-scale increase of long-lasting insecticidal net (LLIN) distribution and indoor residual spray campaigns, both interventions being extremely successful tools for malaria control [3,4]. Nonetheless, the future success of these programmes is threatened by the development of insecticide resistance in the vectors [5]. Resistance is of particular concern since, until now, bed nets can only be treated with pyrethroids because of their rapid knockdown activity, high mosquito mortality ability and extremely low toxicity to humans [6,7]. Thus, although an intact bed net is protective as a physical barrier [8,9], tolerance of malaria vectors to pyrethroids would dramatically reduce the protection afforded by LLINs.

In order to increase the effectiveness of LLINs, net treatments are being developed where nets are treated with a pyrethroid in combination with another active ingredient, such as pyriproxyfen [10,11]. Pyriproxyfen is an insect juvenile hormone mimic that is recommended for vector control by the World Health Organization (WHO) because it is effective at extremely low concentrations, is safe for people [6], and has no cross resistance with other classes of insecticide used for vector control. Its primary effect is to prevent metamorphosis of pupae into adults. In addition, it can sterilise adult mosquitoes, or at least reduce their fecundity and longevity [10,12-15]. Pyriproxyfen has good residual activity in fresh water, with studies on mosquito control showing that it can be effective for 5 to 9 months after initial treatment [16,17].

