### Entomological evaluations

Exposure to mosquitoes will be measured by surveillance with light traps to obtain the primary entomological endpoint [27]. A CDC miniature light trap will be positioned close to a single sleeper protected with a LLIN or PPF-LLIN. Mosquitoes will be identified by microscopy and the numbers of *An. gambiae* s.l., *An. funestus* and other anophelines recorded. The presence of sporozoites in *An. gambiae* s.l. will be identified using an enzyme-linked immunosorbent assay [28] and *An. gambiae* s.l. females will be typed to species by PCR [29]. In the case of *An. gambiae s.s.*, S and M forms will be identified by PCR [30]. Published kdr resistant markers will be typed by PCR [31,32].

6 sentinel clusters will be selected for measurement of the secondary entomological endpoints. Larvae will be collected from a range of breeding sites within each of these sites at the beginning and end of the transmission season in each year of the study. The prevalence of resistance to pyrethroids will be measured using standard diagnostic dose assays with papers impregnated with permethrin, obtained from WHO [33]. To quantify the strength of resistance, a modification of the CDC bottle bioassay will be used in which 3- to 5-day old non-blood-fed female mosquitoes are introduced into 250 mL glass bottles pre-coated with a range of permethrin concentrations. After a 1 hour exposure the mosquitoes are transferred to a holding tube, provided with sugar and water, and mortality recorded 24 hours later. The concentration required to obtain 50% mortality, 24 hours post-exposure is recorded.

To assess the impact of PPF-LLIN on *Anopheles gambiae* egg production and the survival of the larvae that emerge from these eggs, blood-fed mosquitoes will be collected from inside houses via manual aspiration or when exiting houses using exit traps. The female mosquitoes will be transported to the local insectary at Banfora and the number of females that lay eggs, number of eggs hatching and survival to L2 larval stages will be recorded. This will be performed in all 6 sentinel clusters at the beginning and end of the transmission season in each year. In the first round of monitoring, all houses will have standard LLINs and at the final round of monitoring all will have PPF-LLIN.

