## Discussion

The future of malaria vector control in sub-Saharan Africa is threatened by the rapid rise of malaria vectors resistant to pyrethroids [5], currently the only insecticide class available for treating LLINs. Finding solutions to the problem of insecticide resistance is therefore immensely important to ensure that malaria control remains effective. Here we assess whether PPF-LLIN, which contain permethrin and pyriproxyfen, provide additional protection against permethrin-resistant malaria vectors compared with current best practice of LLINs alone. The trial is designed to measure whether the double intervention will provide greater protection against clinical malaria in children by substantially (>25%) reducing transmission.

This is the first clinical trial where a combination of insecticides will be used on one bed net. Unusually the net includes pyriproxyfen which is an insect growth regulator. Unlike conventional insecticides such as permethrin, its main mode of action is not to kill mosquitoes, but to reduce their fertility and fecundity, once they have blood-fed. We hypothesise that the impact of this intervention will be greatest when a large number of people/communities use this net over a wide area. In essence we anticipate that the intervention will have a community-wide impact, reducing the number of mosquitoes within a PPF-LLIN treated area. It is largely for this reason that we have selected a novel study design where this new net is rolled out in a step-wedge fashion to the populations over a 2-year period. We expect that as coverage increases those living in clusters with PPF-LLIN surrounded by other clusters with PPF-LLIN will be better protected against malaria vectors than those on the fringes, where mosquitoes may spill-over from areas without PPF-LLIN. Thus, in the analysis we will consider both where and when people get malaria in order to estimate the efficacy of PPF-LLIN.

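### Parity of An. gambiae is not a valid between-arm measure of mosquito longevity, because pyriproxyfen can change the parous rate without changing survival

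*Protocol article*

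**What the plan says.** Under Study endpoints, Entomological, the protocol article introduces its endpoints as transmission parameters to be estimated in the two arms. Tertiary endpoint (ii) is the parity of An. gambiae, and its stated purpose is "to measure mean population longevity". No caveat is attached.

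Elsewhere the article describes what the added ingredient does to mosquitoes:
- Background, on adults: "it can sterilise adult mosquitoes, or at least reduce their fecundity and longevity".
- Background, on immature stages: "Its primary effect is to prevent metamorphosis of pupae into adults".
- Discussion: "its main mode of action is not to kill mosquitoes, but to reduce their fertility and fecundity, once they have blood-fed". The Discussion also expects a community-wide effect, "reducing the number of mosquitoes within a PPF-LLIN treated area".

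Egg-laying is itself an outcome. Secondary entomological endpoint (ii) is "the fertility and fecundity of adult female *An. gambiae* s.l. collected inside houses in both study arms", and under Entomological evaluations "the number of females that lay eggs, number of eggs hatching and survival to L2 larval stages will be recorded". That work is done in six sentinel clusters at the start and end of each transmission season.

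**The concern.** The article does not define parity. In general entomological usage a female is parous if she has laid eggs at least once, and the parous fraction stands in for age because an older female has had more chances to lay. Comparing arms on that basis needs two conditions: a surviving fed female is equally likely to have laid in each arm, and the inflow of young, not-yet-parous adults relative to the standing population is comparable.

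The protocol gives reasons to doubt both. Permethrin is in both nets at the same concentration, so pyriproxyfen is the stated difference in active ingredient, and it is expected to act on reproduction and on emergence. A female sterilised before her first laying stays nulliparous however long she lives, and so looks young. A fall in emergence removes young females and makes the remaining population look old.

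What is at stake is the mechanism reported. Lost egg-laying could be published as shorter vector life, or a true reduction in longevity, which the Background allows for, could be masked. The Discussion presents this as the first clinical trial of combined insecticides on one net, so such a statement would be noticed.

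**Working it through.** The protocol gives no parous rate, survival rate, cycle length, sterilised share or sample size for parity, so there is no stated figure to reproduce. Everything below is an illustration on assumed inputs.

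**Assumed inputs**
- p, daily survival: 0.80 to 0.90, central value 0.85.
- g, days to first egg-laying: 2 to 4, central value 3.
- s, share of otherwise parous females that have never laid because of pyriproxyfen: 0, 10%, 25%, 50%.
- Survival is identical in both arms throughout.

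**Step 1: no effect on laying.** At steady state the parous fraction is M = p^g and mean life is -1/ln(p). With p = 0.85 and g = 3, M = 0.85^3 = 0.614 and mean life is -1/ln(0.85) = 6.15 days.

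**Step 2: some females never lay.** The observed fraction is M(1 - s), and the inferred daily survival is [M(1 - s)]^(1/g). For s = 10%: 0.614 × 0.90 = 0.553; the cube root is 0.821; inferred life is -1/ln(0.821) = 5.06 days, 18% too short.

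| s | Observed parous fraction | Inferred life (days) | Error, central case | Spurious shortening, full range of p and g |
|---|---|---|---|---|
| 0 | 0.614 | 6.15 | 0 | 0 |
| 10% | 0.553 | 5.06 | -18% | 11-33% |
| 25% | 0.461 | 3.87 | -37% | 24-58% |
| 50% | 0.307 | 2.54 | -59% | 44-77% |

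The s = 0 row also covers a net that only reduces egg numbers or hatching. A female that lays fewer or non-viable eggs is still parous, so there is no bias.

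**Step 3: recruitment falls as well.** If falling emergence shrinks the population by a daily factor λ, the observed fraction is (p/λ)^g × (1 - s). With p = 0.85 and g = 3:
- Numbers falling 25% a week, λ = 0.75^(1/7) = 0.960: s = 10% gives an inferred life of 6.39 days (bias about cancelled); s = 25% gives 4.60 days (still too short).
- Numbers falling 50% a week, λ = 0.50^(1/7) = 0.906: s = 25% gives 6.27 days (about cancelled); s = 10% gives 10.14 days (reversed).

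Once numbers settle at a lower level, λ returns to 1. The upward effect disappears and the Step 2 bias remains.

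Thus the true life is 6.15 days in every central-case calculation, while the figure inferred from parity runs from 2.54 to 10.14 days.

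**The case against.** A reader might infer something stronger: that pyriproxyfen stops egg-laying, so PPF-LLIN is bound to appear to shorten mosquito life, in one arm only. The documents do not support that.
- The Background is hedged. It says sterilisation can occur, or at least a reduction in fecundity and longevity. Counting hatched eggs and larvae implies that some exposed females are expected to lay.
- The same section names blocked emergence as the primary effect. Step 3 shows that this can offset or reverse the bias during roll-out.
- The article expects mosquitoes to spill over between villages with different nets, so exposed females may be caught in either arm. The distortion is differential but not confined to one arm.
- A real longevity effect is among those the Background names, so a lower parous rate need not be an artefact.

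There are further points in the plan's favour. No conversion of parity to life expectancy is proposed. The sizes above assume the affected females never laid at all, whereas one exposed after her first laying stays parous. Sterility is examined directly under a higher-ranked endpoint, so it would be too strong to say that sterilisation and killing cannot be told apart. How parity is scored is a detail that an article may leave to the full protocol.

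These points limit the direction, certainty and importance of the concern. They do not rescue the stated reading. The article itself says what parity is to measure, and no choice of model repairs a marker whose meaning may differ between arms. Two non-survival routes pulling in opposite directions mean that a fall, a rise or no difference could each be misread.

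**Conclusion.** The point holds in a limited form. Parity is confounded by the intervention's stated mode of action and should not be read as longevity between arms. The most likely error is an apparently shorter life under PPF-LLIN, provided an appreciable share of females is sterilised before first laying and numbers are roughly stable. On the assumed inputs its size is 11-33% at 10% sterilised and 24-58% at 25%. It is nil without sterilisation, and uncertain in sign while numbers are falling. None of these figures is an estimate for this trial; they rest on assumed survival, cycle length and sterilised share, and on the usual meaning of parity.

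The consequence is confined to a tertiary endpoint. Clinical incidence, the EIR, the secondary endpoints and the sample sizes are untouched, so the priority is low.

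**What to change.** 1. Restate tertiary endpoint (ii) as the parous rate of An. gambiae, interpreted as the combined effect on egg-laying, survival and recruitment.
2. Delete "to measure mean population longevity" as the purpose of the between-arm comparison.
3. Report the parous rate beside the proportion of collected females that lay in the insectary, so that any loss of egg-laying is visible. State its limits. It comes from six sentinel clusters in four rounds (two seasons, start and end). All houses have LLINs in the first round and PPF-LLINs in the last, so at most the two middle rounds can compare arms at the same time. It can inform the reading of parity but cannot cleanly separate sterility from survival.
4. Do not put the sporozoite rate forward as a clean substitute. It does not depend on egg-laying, but it does depend on infection in people, which the trial expects the nets may change: parasite prevalence and gametocyte carriage are both compared between groups. It is supporting evidence at most.

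The cost is the wording of one endpoint and a sentence of interpretation, with no new samples. What is given up is a direct longevity claim from parity, which the design could not support.

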### Sample size rationale

#### Clinical

LLINs reduce malaria morbidity by approximately 50% [3]. The combined impact of using permethrin, a pyrethroid, and pyriproxyfen is unknown. If the effects were simply additive a mean reduction of 75% could be anticipated for PPF-LLIN (that is, LLINs alone will reduce incidence by 50%, and if we assume the pyriproxyfen alone may reduce the remaining 50% incidence by half, there would be a 75% reduction). However, the effects may be synergistic (for example, by having a mass killing effect). In order to change national guidelines on the use of LLINs we consider that PPF-LLIN should be at least 25% more effective than LLINs. A study of 3- to 60-month old children in Burkina Faso reported an incidence of clinical episodes of malaria of 1.5 episodes/child/year. Malaria incidence data for 2012 from villages in the Banfora region of Burkina Faso indicate the coefficient of variation (CV) for this study will be approximately 0.25. Regarding this study as a simple cluster-randomised controlled trial, assuming CV = 0.25 and that an average of 50 children will be monitored in each cluster for 2 seasons, the study will have 90% power to detect a 25% increase in protection with PPF-LLIN compared to LLINs (that is, a reduction in the incidence of clinical episodes of malaria from 1.5 to 1.125 episodes/child/year) at the 5% level of significance if there are 19.38 clusters in each arm [35]; we thus propose to recruit 20 village clusters into each arm of the study. Adjusting for a coefficient of up to 0.5 for the differences in cluster size (the data from Banfora cited above suggest that this CV will be much lower - approximately 15%), 20 clusters per study arm will still provide the study with 85% power [36].

Assuming prevalence of *P. falciparum* around 30% [37], 20 clusters in each arm and CV = 0.3, the study could detect a 30% reduction of prevalence, with 5% significance and 80% power, between the study arms if longitudinal cohorts for each cluster contain at least 45 children. Assuming mean Hb around 10.5g/dL, 20 clusters in each arm and CV = 0.1, the study could detect a difference of 1.0g/dL in mean Hb, with 5% significance and 80% power, between the study arms if at least 35 children were followed in each cluster .

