A cohort of children will be enrolled to assess the impact of the intervention on malaria. A minimum of 40 children per cluster (range 40 to 75), depending on cluster size, will be randomly selected, stratified by age and invited to participate in the clinical and travel/residence surveys and passive case detection (PCD). The random sample will be stratified by age so that approximately equal numbers of children below and above 36 months will be invited into the study. This was done in case there were marked differences in clinical malaria associated with the different age groups and to ensure balance between the 2 study arms. No distinctions in the sampling scheme will be made regarding gender, ethnic group, medical condition or physical health. Children will only be included on the condition that their carers/parents give witnessed informed written consent. Assurance will also be sought from carers/parents that they expect that the child will remain resident in their village during the transmission season and will not be sent away. If informed consent is not provided for a randomly selected child then replacement children will be randomly selected from those remaining in the village.

The impact of the intervention on the density of malaria vectors and their infection rate with malaria sporozoites will be measured in each village cluster. In each cluster 6 compounds will be selected randomly, from those that have consented to join the study and have at least 4 houses. In each household a room with a single adult male sleeper will be selected if the room owner/sleeper provides witnessed, verbal consent.

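### The prevalence requirement of 45 children per cluster omits the extra-cluster term used for the primary endpoint (about 50 are needed with it), and the enrolment minimum of 40 is below 45

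*Protocol article*

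**What the plan says.** In the Sample size rationale (Clinical), the primary endpoint is planned for "a reduction in the incidence of clinical episodes of malaria from 1.5 to 1.125 episodes/child/year", with 90% power, "assuming CV = 0.25 and that an average of 50 children will be monitored in each cluster for 2 seasons". The result is given as "at the 5% level of significance if there are 19.38 clusters in each arm", which is rounded up to 20.

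The next paragraph takes a prevalence "around 30% [37], 20 clusters in each arm and CV = 0.3", and says that "the study could detect a 30% reduction of prevalence, with 5% significance and 80% power" "if longitudinal cohorts for each cluster contain at least 45 children". For haemoglobin, 80% power for a difference of 1.0 g/dL is claimed "if at least 35 children were followed in each cluster".

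Study area and participant eligibility sets the cohort size: "A minimum of 40 children per cluster (range 40 to 75"), depending on cluster size. The Design section adds, where possible and at every survey except the first, an average of 50 children per cluster from outside the cohort.

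**The concern.** Two things do not fit together. First, the primary and prevalence calculations stand side by side and rest on the same 20 clusters per arm, but appear to use different versions of the formula. The version with one added cluster allows for estimating between-cluster variation from a small number of clusters; leaving it out makes the requirement look smaller. Second, the prevalence power is conditional on every cohort having at least 45 children, while the enrolment rule accepts 40.

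At stake is whether the 80% quoted for a secondary endpoint is supported by the planned cohort. The primary endpoint and the number of clusters are not in question.

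**Working it through.** **Formula.** The protocol prints none, so the unmatched cluster formula was tested against its own figures:

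c = [1 +] (z₁ + z₂)² × [within-cluster variance / m + k²(μ₀² + μ₁²)] / (μ₀ − μ₁)²

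Here c is clusters per arm, m is children (or child-seasons) per cluster and k is the between-cluster CV. The 5% level is taken as two-sided, and the trial is treated as parallel, as the protocol does for the primary endpoint.

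**Step 1: reproduce the primary figure.** Inputs from the Sample size rationale: rates 1.5 and 1.125, k = 0.25, m = 50 × 2 = 100, 90% power, so (1.960 + 1.282)² = 10.507.

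- Within: (1.5 + 1.125)/100 = 0.02625
- Between: 0.0625 × (2.25 + 1.2656) = 0.21973
- Squared difference: 0.375² = 0.140625
- 10.507 × 0.24598 / 0.140625 = 18.38; with the added cluster, **19.38**

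The match to the printed 19.38 shows that the term was used.

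**Step 2: prevalence at the stated 45.** Inputs from the same section: 0.30 against 0.30 × 0.70 = 0.21, k = 0.3, 80% power, so (1.960 + 0.842)² = 7.849.

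- Binomial variances: 0.21 + 0.1659 = 0.3759; at m = 45, 0.3759/45 = 0.00835
- Between: 0.09 × (0.09 + 0.0441) = 0.01207
- Squared difference: 0.09² = 0.0081
- 7.849 × 0.02042 / 0.0081 = 19.79; with the added cluster, 20.79

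So 45 children fit within 20 clusters only without the term.

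**Step 3: solve for m at 20 clusters.**

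- Without the term: 0.3759 / (20 × 0.0081/7.849 − 0.01207) = 43.9
- With the term: 0.3759 / (19 × 0.0081/7.849 − 0.01207) = 49.9

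With a pooled binomial variance the values are 44.3 (rounding up to 45) and 50.4. The printed 45 therefore corresponds to the version without the term; the primary's version gives 50 or 51.

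**Step 4: power at 20 clusters per arm.**

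| Children examined per cluster | Clusters needed, with term | Power, with term | Power, without term |
|---|---|---|---|
| 40 (every cluster) | 21.80 | 76.3% | 78.4% |
| 45 | 20.79 | 78.4% | 80.4% |
| 50 | 19.98 | 80.0% | 82.0% |

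A noncentral t calculation on 38 degrees of freedom gives the same 76.3%, 78.4% and 80.0% as the column with the term.

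**Step 5: absence at the survey.** The protocol gives no absence rate. Assuming 0%, 10% or 20% absent from a cohort averaging 50 leaves 50, 45 or 40 examined, and so 80.0%, 78.4% or 76.3% with the term.

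**The case against.** The strongest reply is that the plan still reaches its target. A minimum is not an average: the protocol plans on 50 per cluster, which gives 80.0% with the stricter formula. If half the clusters had 40 children and half 60, power would be 79.4%; with sizes spread evenly from 40 to 75 it would be 81.5%. The gap at 45 is 1.6 points, within the roughness of the inputs: with the term and 45 children, a prevalence of 33% gives 80.4%, though 29% gives 77.6%. This stands, and it rules out saying that 80% power is not delivered.

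The non-cohort survey children also count in the plan's favour. The secondary endpoints are defined for children in the two arms, not only for the cohort; with about 100 per cluster, power is 87.7%. That stands in part. These children are promised only where possible, a cluster with little more than 50 eligible children has few left outside its cohort, and the sample-size statement rests expressly on the longitudinal cohorts. Drop-outs are replaced in May 2015, but not during a surveillance period.

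A reader might infer that the haemoglobin figure of 35 has the same fault, or that 20 clusters cannot reach 80% for it. The documents do not support this. They give neither the within-cluster SD nor the direction of the 1.0 g/dL difference. Assuming an SD of 1 to 2 g/dL, with the term and 35 children, power is 83.1–85.9% for 10.5 against 9.5, 79.7–82.5% for 10 against 11, and 76.3–79.0% for 10.5 against 11.5. The minimum of 40 also exceeds 35, so the enrolment rule does not conflict with it.

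**Conclusion.** The point holds for prevalence, at minor severity. The protocol's two calculations use different versions of the formula; with the one used for the primary endpoint, 80% power needs about 50 examined cohort children per cluster, not 45. The shortfall is 1.6 points at 45 and 3.7 points if every cluster were at 40. The conflict between the minimum of 40 and the condition of at least 45 does not depend on the formula: with every cluster at 40, power is below 80% either way.

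The planned average of 50 just meets the target, so this is a misstated requirement with no margin for absence, not proof of an underpowered endpoint. These figures assume a two-sided 5% level, a parallel comparison, equal cluster sizes and cohort children only. No conclusion is drawn about haemoglobin power.

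**What to change.** In the Sample size rationale, use the same formula for prevalence as for the primary endpoint. Either restate the requirement as about 50 examined children per cluster on average, or keep 40–45 and state about 76–78% power. Say whether the non-cohort survey children count towards this number; if they do not, acknowledge that an average of 50 leaves no room for absence.

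Reconcile the minimum of 40 in Study area and participant eligibility with the condition of at least 45. Raising the minimum is feasible on the protocol's own terms, since each cluster must have more than 50 children in the age range; rewording the condition as an average would also do.

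The haemoglobin power should not be restated at another value without the SD and direction. Restating the figures costs only wording and a slightly less favourable number; raising the minimum would mean enrolling a few more children in the smallest clusters. The 20 clusters per arm stay as they are.
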